### Statistical analysis

A flow of participants through the trial will be summarised in a Consolidated Standards of Reporting Trials (CONSORT) diagram. Descriptive statistics of baseline clinical and socio-demographic characteristics will be presented to describe the study sample and to ascertain comparability of the randomisation groups.

Data from the internal pilot phase of the study will be assessed against predefined/pre-agreed stop/go criteria to inform the decision as to whether to continue the trial to the ‘main’ phase. The proposed ‘traffic light’ (stop/go) criteria are based on descriptive statistics summarising recruitment, retention and adherence.

The primary analysis will be carried out under the intention-to-treat (ITT) principle, analysing participants as randomised without the imputation of missing data. Kaplan-Meier survival curves will be plotted to depict the probability of symptom resolution over time. Symptom resolution over the 14 days of follow-up will be compared between children allocated to immediate oral antibiotics and those allocated to each of the other treatment groups using a Cox proportional hazards regression model, adjusted for age (stratification variable). The primary outcome will also be analysed using an Accelerated Failure Time (AFT) model, which has previously been recommended for studies of resolution of infectious diseases as previous research has suggested that symptoms of AOM will be resolved in 90% of children by day 8.

The proportion of participants in the immediate topically and delayed orally administered antibiotics arms who achieve symptom resolution within 3 days will be compared (separately) to those in the immediate orally administered antibiotics arm. The absolute difference will be calculated and reported alongside the associated confidence interval, it will then be reported as to whether or not the lower limit of the confidence interval lies within the maximum unimportant difference.

Analysis of secondary outcomes will utilise regression models appropriate for the nature of the outcome measure (i.e. logistic regression for binary outcomes, Poisson or negative binomial regression for count data).

The primary analysis model will be repeated but with the outcome of symptom resolution being defined as when all symptoms are rated as being ‘normal/none’, ‘very slight problem’ or ‘slight problem’ (compared to the primary outcome of symptom resolution being defined as all symptoms being rated as ‘normal/none’ or ‘very slight problem’). The primary analysis will also be repeated under the per-protocol approach (rather than ITT). The sensitivity of the primary analysis to the impact of missing data will also be explored by repeating the analysis after the imputation of missing primary outcome data. The primary analysis and AFT model will be repeated with additional adjustment for any prognostic variable showing a marked imbalance at baseline (ascertained using descriptive statistics). Baseline characteristics will be investigated as potential treatment effect moderators, this will be done by including treatment group by moderator interaction terms into the primary analysis model (individually).

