#### Intervention description

Arm 1: (control) current usual care – orally administered amoxicillin suspension three times daily for 7 days (or orally administered clarithromycin twice daily for 7 days if allergic to penicillin).

Arm 2: (intervention) antibiotic drops, to be instilled three times daily into the discharging ear. Parents will be given written advice regarding how to administer the drops. This will include: (1) cleaning the outer ear of discharge that can be easily removed with a tissue; (2) tilting the child’s head to one side (to approximately 90°) when applying the eardrops; and (3) maintaining the tilt for a few minutes to improve penetration of the drops.

Arm 3:(intervention) a ‘delayed’ prescription for orally administered amoxicillin suspension antibiotics three times daily for 7 days (or orally administered clarithromycin twice daily for 7 days if allergic to penicillin). Parents will be given written advice to delay the prescription will consist of: (1) advising that the prescription is only ‘dispensed’ at a pharmacy if symptoms worsen or are not starting to improve by 4 days; and (2) safety-netting advice regarding the symptoms that should prompt review consultation (increasing pain, high temperatures, headaches, irritability or reduced feeding).

All groups will also receive standard advice to complete the antibiotic course and how to manage pain, fever and other symptoms (e.g. use of paracetamol/ibuprofen).

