### Sample size

Our previous trial compared immediate with delayed antibiotic use [1]. Children with AOMd took a median of 3 days (interquartile range (IQR) 2, 4) to achieve the REST primary outcome. Our PPI advised a 1.25-day non-inferiority margin (equivalent to an absolute difference in cure rate of 19.5% at 3 days). A two-group non-inferiority trial normally assumes a 2.5% one-sided Type I error. Using a 1.25% Type I error to detect non-inferiority for two comparisons with 90% power, complete outcome data needed for 106 per arm is 399 with 20% attrition.

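### Non-inferiority is to be judged on time to resolution with a 1.25-day margin, but the only result compared with a margin is the day-3 proportion

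*Protocol article*

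**What the plan says.** The Outcome measures section makes time to resolution the primary outcome, and the Discussion says the non-inferiority conclusion will rest on it.

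The Sample size section sets the margin in days, "Our PPI advised a 1.25-day non-inferiority margin", and then calls it "equivalent to an absolute difference in cure rate of 19.5% at 3 days". The planning data are these: "Children with AOMd took a median of 3 days (interquartile range (IQR) 2, 4) to achieve the REST primary outcome". The size follows: "Using a 1.25% Type I error to detect non-inferiority for two comparisons with 90% power", with "complete outcome data needed for 106 per arm is 399 with 20% attrition".

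The Statistical analysis section compares arms over 14 days "using a Cox proportional hazards regression model, adjusted for age (stratification variable") and adds an AFT model. Neither is given a margin. The difference in the proportion resolved within 3 days is then calculated with a confidence interval, and "it will then be reported as to whether or not the lower limit of the confidence interval lies within the maximum unimportant difference". That section puts no number on the maximum unimportant difference; the 19.5 points of the Sample size section is the natural reading.

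In the delayed arm (Intervention description), parents are told to have the prescription dispensed "at a pharmacy if symptoms worsen or are not starting to improve by 4 days".

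**The concern.** In a non-inferiority trial the margin and the test against it carry the conclusion. Here the outcome and margin are in days, the primary model gives a hazard ratio, and the one comparison with a margin is a difference in proportions at a single day. A reader cannot tell which result decides. The results could also disagree, because 1.25 days and 19.5 points at day 3 coincide only for particular distributions. The day-3 check discards what the daily diary records from day 4 to day 14. In the delayed arm it also falls before the 4-day point at which lack of improvement triggers dispensing.

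**Working it through.** **Inputs from the Sample size section.** Median 3 days, IQR 2 to 4; margins 1.25 days and 19.5 points; one-sided alpha 1.25% (z = 2.2414); power 90% (z = 1.2816); 106 complete per arm. The Statistical analysis section adds 90% resolved by day 8, stated for AOM in general. The article states no distribution, so the shapes below are assumptions.

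1. *The plan's own figures.* The inflation reproduces: 106/0.80 = 132.5, so 133 per arm, and 3 × 133 = 399. The 106 does not follow from the day-3 margin with the printed inputs. n = (2.2414 + 1.2816)² × 2p(1−p)/0.195² gives 164 at p = 0.50 and 123 at p = 0.75. It gives 105 to 107 only at p of about 0.795 to 0.80, which exceeds the 75% at day 3 that an upper quartile of 4 days allows. On other scales, 106 needs an SD of about 2.58 days for a mean difference of 1.25, or a hazard-ratio margin of about 0.616. Neither is printed.

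2. *Is 1.25 days equal to 19.5 points at day 3?* Scale the median from 3 to 4.25 days and take 50% minus the proportion then resolved by day 3.
   - Weibull with shape k: difference = 0.5^((3/4.25)^k) − 0.5. For k = 1 (exponential), 0.5^0.706 − 0.5 = 0.113. For k = 1.85, 0.5^0.525 − 0.5 = 0.195. For k = 2.27 (fitted to the IQR), 0.5^0.454 − 0.5 = 0.230.
   - Log-normal: difference = Φ(ln(4.25/3)/σ) − 0.5, with ln(4.25/3) = 0.348. For σ = ln(4/2)/1.349 = 0.514 (fitted to the IQR), Φ(0.678) − 0.5 = 0.251. For σ = ln(8/3)/1.2816 = 0.765 (90% resolved by day 8), Φ(0.455) − 0.5 = 0.176.

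   The stated equivalence therefore holds for a Weibull shape near 1.85, among others, but not in general.

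3. *Can a Cox margin be read off?* Under the Weibull the hazard ratio is (3/4.25)^k: 0.706, 0.525 or 0.454 for the three shapes. The range is too wide for a reader to supply the margin.

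4. *Power of the day-3 check with identical arms.* Φ(0.195/√(2p(1−p)/106) − 2.2414).
   - p = 0.50: SE = 0.0687, Φ(2.839 − 2.241) = 72.5%.
   - p = 0.75: SE = 0.0595, Φ(3.278 − 2.241) = 85.0%.

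5. *Comparison with a test in days.* I simulated identical arms with 106 per arm, median 3 and times truncated at 14 days. The restricted-mean difference was tested against 1.25 days, and the day-3 difference against 19.5 points.
   - Weibull 1.85 or 2.27, or log-normal 0.514: restricted mean passes over 99%, day 3 about 73 to 74%. The two verdicts differ in roughly a quarter of trials.
   - Log-normal 0.765: about 79% and 73 to 74%, differing in about a fifth.
   - Exponential: about 58% and 73%. This shape implies an IQR of about 1.2 to 6.0, which does not fit the stated 2 to 4, so it is an outer bound.

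**The case against.** The strongest reply has five parts.

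- *The day margin is tested, by a declared proxy.* This is right. A reader might infer that 1.25 days is never tested at all, but the article declares the two margins equivalent and checks one of them. What remains is that the equivalence rests on an unstated distribution.
- *The full protocol or the analysis plan may give a hazard-ratio or time-ratio margin.* It may, and a missing conversion alone would be no finding. The mismatch between the margin, the analysis that checks it and the stated basis of the conclusion is in the printed text. Nor does the article formally name day 3 as the decision rule; that is inferred from its being the only check against a margin.
- *Delayed antibiotics can start before day 4.* This is also right: the advice allows dispensing whenever symptoms worsen. It is tempting to say that day 3 compares no antibiotic with antibiotic, but the article gives no early-dispensing rate. Non-proportional hazards in this arm are likewise plausible but not shown.
- *A test in days is not always more powerful.* Agreed. The gain is large for shapes near the stated IQR, small with the longer tail, and reversed for the exponential. Day-3 power does fall to about 20% under a true 10-point deficit at 50% resolution, but a time-scale test also loses power under such a deficit, so that figure is no fair comparison.
- *Only 22 children were recruited and recruitment has closed (Trial status).* No margin test on those data could be conclusive. This limits the practical consequence, but it does not make the printed rule coherent for reporting or for reuse of the design.

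**Conclusion.** The point holds in this form: the article places the conclusion and margin on the time scale but applies a margin only to the proportion resolved by day 3. The proxy corresponds to anything from about 11 to 25 points under the distributions tried. As printed it has about 72 to 85% power for 50 to 75% resolution by day 3, against 90% stated. Those powers assume 106 complete per arm, no true difference and a 19.5-point margin. For the delayed arm, day 3 captures only the part of the strategy before the 4-day non-improvement trigger.

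It might be inferred from the first step of the working that 106 per arm is an error. The documents do not show that, because the control rate, SD or hazard ratio behind it is not printed.

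**What to change.** Name one decisive non-inferiority analysis of time to resolution over 14 days, for each arm against immediate oral antibiotics, using the 97.5% two-sided confidence interval (one-sided 1.25%). Either choice would do:

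- The age-adjusted difference in restricted mean time to 14 days, with non-inferiority declared if the upper limit is below 1.25 days. State that the margin is then read as a mean difference. This is a choice, because scaling the median by 1.25 days gives a restricted-mean difference of about 1.30 to 1.41 days in the scenarios above.
- The AFT model already planned, with a stated time-ratio margin of 4.25/3 = 1.42. This equals 1.25 days only if the control median is 3; at a median of 4 it would allow 4 × 0.4167 = 1.67 days.

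Make the Cox model and the day-3 difference supportive, with no separate verdict. Delete the claim of equivalence in the Sample size section, or state the distribution behind it. Reconcile the day-3 time point with the 4-day dispensing advice in the text; no change to the advice is proposed here.

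The cost is wording only, since the daily questionnaire already supplies the data. The downside is that power depends on the tail: for the restricted mean, over 99% for shapes near the stated IQR, about 79% if 90% resolve by day 8, and about 58% if times are exponential.

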### Participants and eligibility

Eligible participants are children aged ≥ 12 months to < 16 years whose parents/legal guardians are seeking primary medical care for acute-onset unilateral otorrhoea as the presenting symptom of recent-onset (≤ 7 days) AOM. Detailed inclusion and exclusion criteria are detailed in Table 1.

**Table 1 Tab1:** Inclusion and exclusion criteria

Patient selection criteria	
**Inclusion criteria (child must meet all criteria):**	1. Children aged ≥ 12 months to < 16 years 2. Presenting with recent-onset (≤ 7 days) unilateral AOM with recent-onset (≤ 7 days) otorrhoea currently visible (or seen by parent/legal guardian ≤ 24 h) 3. Child attending with parent/legal guardian who is legally able to give consent in person 4. Parent/legal guardian willing and able to administer eardrops 5. Parent/legal guardian willing, able and available to complete the daily SRQ and received regular telephone calls from the study team
**Exclusion criteria (excluded if child meets any criterion at the time of entry):**	1. Symptoms/signs suggestive of bilateral AOM/AOMd 2. Child has symptoms/signs suggestive of serious illness and/or complications, e.g. mastoiditis and/or requires immediate hospitalisation 3. Child requires immediate orally administered antibiotics (e.g. for another infection or AOMd considered severe) 4. As per NICE guidelines [12], a child at high risk of serious complications: • Significant immunosuppression • Heart, lung, renal, liver or neuromuscular disease (defined as requiring ongoing inpatient or outpatient care from specialist teams) co-morbidities • Trisomy 21 (Down’s syndrome), cystic fibrosis or craniofacial malformation, such as cleft palate (these children are known to be at higher risk of AOM) 5. Grommet (ventilation tube) in situ in the ear with otorrhoea 6. Currently taking orally (for a respiratory tract infection) or topically administered (in the affected ear) antibiotics 7. Allergy to ciprofloxacin 8. Allergy to penicillin/anaphylaxis to another beta-lactam agent and allergy to clarithromycin 9. Child has taken part in any research involving medicines within the last 90 days 10. Child has already participated in this trial

*AOM* acute otitis media, *SRQ* Standard Recovery Questionnaire

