#### Clinician-recorded outcomes: baseline data collection form and contact form

During the consultation, clinicians will complete a baseline data collection form and contact detail form for all eligible participants. The baseline data collected includes acute clinical data and any relevant medical history relating to AOMd incidence.

A contact details form will record information from the parent/legal guardian including name, address, telephone number and availability to take calls from the research nurse.

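### Covariates beyond age are to be chosen by observed baseline imbalance, and the day-3 difference, the only result set against a margin, names no adjustment; a short list fixed in advance would do modestly better

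*Protocol article*

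**What the plan says.** Under Statistical analysis, the protocol article makes the primary analysis an intention-to-treat Cox model adjusted for age, the only stratification factor. An accelerated failure time (AFT) model is added. Among the repeat analyses later in that section, both models are to be "repeated with additional adjustment for any prognostic variable showing a marked imbalance at baseline (ascertained using descriptive statistics". No covariates are listed and no size of imbalance is given.

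The same section describes a comparison of the proportions resolved within 3 days. "The absolute difference will be calculated and reported alongside the associated confidence interval", and the lower limit is then set against the largest difference regarded as unimportant. No covariate is mentioned for this comparison. It is the only place in the article where a result is compared with a margin, and Sample size gives the margin partly on that scale: "1.25-day non-inferiority margin (equivalent to an absolute difference in cure rate of 19.5% at 3 days".

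On what could be adjusted for, the section on clinician-recorded outcomes says: "The baseline data collected includes acute clinical data and any relevant medical history relating to AOMd incidence". Table 1 admits children "Presenting with recent-onset (≤ 7 days) unilateral AOM".

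**The concern.** In a randomised trial, baseline differences between arms arise by chance. What a covariate contributes depends on how well it predicts outcome, not on whether it happens to differ between arms. A rule driven by observed imbalance therefore leaves out strong predictors that are balanced and may bring in weak ones that are not. It also leaves the choice of covariates open until the arm comparison at baseline has been seen.

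Strong predictors are plausible here. Children may enter up to 7 days after onset, while the planning data have resolution at a median of 3 days. Time already spent ill and severity at presentation could well affect how soon a child recovers. Neither is in the primary model, and the day-3 difference as worded leaves out even age. The stake is the width of the day-3 confidence interval relative to a 19.5-point margin.

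**Working it through.** **Inputs from Sample size.** Margin 0.195 at day 3; one-sided error 1.25% per comparison ("A two-group non-inferiority trial normally assumes a 2.5% one-sided Type I error", then "Using a 1.25% Type I error to detect non-inferiority for two comparisons with 90% power"); 106 per arm with complete data; 20% attrition. The control cure rate at day 3 is not stated. "Children with AOMd took a median of 3 days (interquartile range (IQR) 2, 4" puts it at about 50% to 75%, because the median is day 3 and the upper quartile is day 4.

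**The plan's own figure.** The inflation reproduces: 106/0.8 = 132.5, so 133 per arm, and 3 × 133 = 399. The 106 was checked with

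n = (z₀.₉₈₇₅ + z₀.₉₀)² × 2p(1−p)/0.195², where (2.2414 + 1.2816)² = 12.41.

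- p = 0.50: 12.41 × 0.500/0.038025 = 163.2, so 164 per arm.
- p = 0.75: 12.41 × 0.375/0.038025 = 122.4, so 123 per arm.
- p = 0.80: 12.41 × 0.320/0.038025 = 104.4, so 105 per arm.

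So 106 does not follow from the stated inputs unless day-3 cure is near 80%. That is a separate matter. Here it only means that the gain must be shown over a range of cure rates.

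**Gain from adjusting the day-3 difference.** The documents give no R² for baseline covariates, so R² is an assumption, taken from 0.05 to 0.20. With no true difference and 106 per arm:

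SE = √[2p(1−p)(1−R²)/106]; half-width = 2.2414 × SE; power = Φ(0.195/SE − 2.2414).

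Example, p = 0.50: unadjusted SE = √(0.5/106) = 0.0687, and power = Φ(2.839 − 2.241) = 72.5%. With R² = 0.10, SE = 0.0652 and power = 77.4%.

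| R² | Interval narrower by | Power, p = 0.50 | Power, p = 0.75 | Power, p = 0.80 |
|---|---|---|---|---|
| 0 | – | 72.5% | 85.0% | 90.5% |
| 0.05 | 2.5% | 74.9% | 86.9% | 91.9% |
| 0.10 | 5.1% | 77.4% | 88.8% | 93.3% |
| 0.20 | 10.6% | 82.5% | 92.3% | 95.8% |

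At p = 0.50 the half-width falls from 15.4 points to between 15.0 and 13.8. At p = 0.80 it falls from 12.3 to between 12.0 and 11.0. The smallest gain in the table is 91.9 − 90.5 = 1.4 points and the largest is 82.5 − 72.5 = 10.0 points.

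**How much an imbalance trigger recovers.** The article applies its trigger to the Cox and AFT models. To see how such a rule performs, it was simulated on the day-3 difference: 20,000 trials, 106 per arm, one prognostic covariate, adjustment only if the standardised imbalance exceeds 0.25 (an assumed threshold, since the article gives none).

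| Setting | Never adjusted | Adjusted if imbalanced | Always adjusted |
|---|---|---|---|
| Cure 50%, R² 0.12 | 73.5% | 74.3% | 78.6% |
| Cure 80%, R² 0.08 | 90.3% | 90.7% | 92.6% |

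The trigger fires in about 7% of trials per covariate. The theoretical value is 2[1 − Φ(0.25/√(2/106))] = 6.9%. In the first setting it recovers 0.8 of the 5.1 points available.

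**Cox model.** The factor √(1−R²) does not carry over to a log hazard ratio, whose standard error is governed by the number of events. Simulating 106 per arm with no treatment effect and a covariate with an assumed log hazard ratio of 0.4 or 0.6 per SD, the mean standard error moved from 0.139 to 0.140 on adjustment. It did not fall. Adjustment gains power in a Cox model because the conditional hazard ratio lies further from 1 than the marginal one when there is an effect.

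**The case against.** The strongest reply is that the primary analysis is sound as written: a Cox model fixed in advance and adjusted for the stratification factor. The imbalance rule governs only one repeat in a list of sensitivity analyses. This stands. A reader might infer that the primary model can be picked after seeing the data, and the article does not support that.

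Second, a reader might take the day-3 difference to be the stated basis of the verdict, and to be stated as unadjusted. Both are inferences. The article calls the Cox model primary, and its Discussion rests non-inferiority on time to resolution. The day-3 difference is singled out here only because no other result is set against a margin. On adjustment the article is silent, and an analysis plan that is not shown may supply it. What remains is the contrast within one section: age is named for the Cox model and nothing is named for the difference.

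Third, it might be inferred that fixed adjustment would narrow every interval. For the hazard ratio it would not, as shown above.

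Fourth, R² has no source in the article, and the article names neither days since onset nor a severity score as recorded baseline items. Eligibility needs only a 7-day threshold, and the symptom questionnaire runs from day 1. This also stands, and it limits both the size of the claim and the wording of the fix.

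The reply does not rescue the trigger. It is stated outright. An analysis plan could give it a threshold, but choosing covariates by observed imbalance would remain.

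**Conclusion.** The point holds in a limited form. The article commits to a poor rule for choosing covariates beyond age. As worded, it also leaves the one comparison made against a margin without even the stratification factor. Nothing here biases the primary result. The cost is precision on the day-3 difference: an interval about 2.5–11% wider than it need be, and about 1–10 points of power, smallest at a cure rate near 80% and largest near 50%. These figures assume an R² of 0.05–0.20, 106 per arm with complete data, one-sided error of 1.25% and no true difference. The share recovered by a trigger also rests on the assumed threshold of 0.25 SD.

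**What to change.** Replace the imbalance trigger with a short list of prognostic covariates named before the arms are compared: age stratum, plus days since onset and presenting severity where the baseline form records them. Use this list in the Cox and AFT models whatever balance is observed. Estimate the day-3 risk difference by standardisation from a model with the same covariates. Keep the age-only Cox model as a sensitivity analysis.

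This changes analysis wording and needs no extra patients. There are two conditions. The baseline form must be checked for the two clinical items, and the list cut to what it holds. The report must also say that the Cox hazard ratio is then conditional on the added covariates, which is a small loss in ease of interpretation.
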